### Sample size

The sample size was calculated based on the primary hypothesis that KOKU combined with PC (IG1) will increase mean daily step count (first primary outcome) 6 months postoperatively, compared with usual care (CG). Based on previous observational studies, a mean daily step count of 5,000 ± 3,000 steps for the preoperative PA was assumed [79–83]. An increase of 1,500 steps per day in the IGs was assumed, which has been associated with an approximately 20% reduction in all-cause mortality risk among older adults [84, 85]. Under these assumptions, 64 participants per group are required to achieve a statistical power of 80% at a two-sided significance level of 5% using a *t*-test for independent samples. For the subordinated primary outcome (mean daily walking distance), which will be tested in a hierarchical order, a similar effect size is expected. Accounting for an anticipated dropout rate of 10%, the required sample size increases to 71 participants per group, resulting in a final total sample size of 213 participants.

### Randomization and blinding

After the 6-week postoperative assessment (T2), participants will be randomized to one of three study arms in a 1:1:1 allocation ratio using permuted block sizes, stratified by type of post-acute rehabilitation (outpatient, inpatient, or none). The random allocation sequence will be generated automatically using the web-based tool randomizer.at (Institute for Medical Informatics, Statistics and Documentation, Medical University of Graz, Austria; https://www.randomizer.at). Allocation concealment will be ensured through this centralized, Good Clinical Practice-compliant web-based tool. Randomization will be performed exclusively by authorized study personnel with individual access credentials.

All primary and secondary outcome assessments will be undertaken by assessors blinded to group allocation. Other prespecified outcomes, including training adherence and intervention acceptability, will be collected using self-completed questionnaires provided to participants after the final 6-month postoperative assessment (T3). These will be completed at home and returned to the study center by mail using prepaid envelopes.

Usage data of the KOKU app will be downloaded from the tablets of participant in the IGs by assessors only after completing of the on-site T3 assessment.

AEs will be documented by the unblinded coaches during the intervention period (for participants of both IGs) and at the end of the intervention period (for all participants). At T3, AEs will also be recorded by blinded assessors, but only at the end of the visit, after all other on-site assessments have been completed.

Processing of the DMOs after return of the IMU will be conducted at T3 by blinded study personnel who are not involved in the on-site T3 assessment.

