#### Secondary outcomes

Secondary DMOs will be derived from the IMU recordings using also the validated Mobilise-D computational pipeline, applying the same valid-measurement criteria as for the primary outcomes: walking duration; number of WBs (all, > 10 s, > 30 s, > 60 s); WB duration and 90th percentile (P90) in WB duration; walking speed and P90 walking speed in WBs > 10 s and > 30 s; stride length (WBs 10–30 s and > 30 s); stride duration (all WBs and > 30 s); cadence (all WBs and > 30 s) and P90 cadence (WBs > 30 s); and bout-to-bout variability for WB duration (all WBs), walking speed and stride length (WBs > 30 s), cadence and stride duration (all WBs). Detailed definitions and the daily and weekly calculation procedures of these DMOs are provided elsewhere [34].

Self-reported daily-life mobility will be assessed using the Life-Space Assessment [57, 58] and the UCLA Activity Score [59].

Physical capacity will be measured using the 6-Minute Walk Test (6MWT) [60], the Timed Up and Go (TUG) [61], the 30-Second Chair Stand Test, and the 4-Meter Gait Speed Test [62]. The 6MWT and TUG will be instrumented with the mTEST3 system (mHealth Technologies srl, Bologna, Italy), a CE-certified sensor-based motion analysis system, to measure spatiotemporal gait parameters during the 6MWT (e.g., asymmetry, step length) and segments of movements during the TUG (e.g., sit-to-stand, walking, turning, stand-to-sit). Changes in self-perceived walking ability will be assessed with a 7-item Global Rating of Change scale [63].

Hip pain and function will be assessed using the Oxford Hip Score [64]. Back pain will be measured using the Oswestry Disability Index [65, 66].

Psychological factors will be evaluated using the Short Falls Efficacy Scale-International [67], the conscientiousness dimension of the Big Five Inventory-2 [68], and the Behavioral Regulation in Exercise Questionnaire (motivation regulation in PA) [69, 70].

Self-reported health status will be assessed using the EuroQol 5-Dimension 5-Level and the EuroQol Visual Analogue Scale [71].

Falls will be prospectively self-monitored by participants for each week after T2 assessment using fall calendars, which include documentation sheets to record the date, time, and location of the fall, the activity preceding the fall, and any fall-related injuries.

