### Harms and safety monitoring

Postoperative complications occurring between the preoperative baseline assessment (T1) and the 6-week postoperative assessment (T2) will be recorded at the on-site T2 visit.

Adverse events (AEs) will be documented for the period from the 6-week postoperative assessment (T2) to the 6-month assessment (T3), regardless of any causal relationship to the interventions.

These will be recorded by telephone interview conducted by the coaches at the end of the intervention period and at the very end of the on-site 6-month assessment (T3) by assessors. In addition to systematically collected postoperative and AEs at scheduled assessments, interim events spontaneously reported by participants (e.g., via telephone calls) will also be documented as reported.

The severity of complications and AEs will be classified into: (1) mild = transient and easily tolerated events, causing no or minimal interference with activities of daily living (ADLs) and not requiring medical intervention; (2) moderate = events causing noticeable interference with ADLs and/or requiring minimal or noninvasive medical intervention; (3) severe = events resulting in marked limitation of ADLs, requiring medical intervention or hospitalization, including life-threatening events and death.

An independent Data Safety Monitoring Board (DSMB) will oversee participant safety and trial conduct. The DSMB will consist of an orthopedic surgeon, a geriatrician, and a biometrician. It will regularly review accumulating reports of AEs, assess their causal relationship with the interventions and severity classification, and make recommendations on potential modifications or discontinuation of the study. The DSMB will operate under a written charter specifying its roles, responsibilities, and decision-making processes.

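### Coach documentation of adverse events during the intervention covers only the two intervention groups, which puts between-arm AE frequencies at risk of ascertainment bias

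*Protocol article*

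**What the plan says.** Two sections of the Protocol article describe how AEs are collected.

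Randomization and blinding says that "AEs will be documented by the unblinded coaches during the intervention period (for participants of both IGs", and the sentence goes on "and at the end of the intervention period (for all participants". It then adds: "At T3, AEs will also be recorded by blinded assessors, but only at the end of the visit".

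Harms and safety monitoring sets the window: "Adverse events (AEs) will be documented for the period from the 6-week postoperative assessment (T2) to the 6-month assessment (T3", whatever the cause. It names the systematic collection points, beginning with: "These will be recorded by telephone interview conducted by the coaches at the end of the intervention period". The second is the on-site T3 visit. It adds that "interim events spontaneously reported by participants (e.g., via telephone calls) will also be documented as reported". It says nothing of a channel for the intervention groups only. Table 2 marks complications and AEs at T2, during the intervention and at T3, without distinguishing arms.

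Falls have a route of their own under Secondary outcomes: "Falls will be prospectively self-monitored by participants for each week after T2 assessment using fall calendars".

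Statistical analysis plans absolute and relative frequencies for safety from randomization onward. It states no between-arm safety test and does not mention the source of events.

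**The concern.** The more often, and the sooner, a participant is in touch with someone who writes events down, the more minor events are recorded. The plan counts AEs regardless of cause, and its mild category is for transient events that need no medical care. Those are the events most easily forgotten by a later call. If one route is open to the intervention groups and closed to controls, arms with the same true risk can show different frequencies.

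Three uses of the data could be touched.

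- **The safety table.** The exercise app, or the app with coaching, could look less safe than usual care because of recording alone.
- **The safety board.** It reviews accumulating AE reports and may recommend changes or discontinuation. During the 12 weeks those reports would come through an unequal channel.
- **The imputation model.** Post-randomization AEs are listed as intercurrent events, and relevant intercurrent events enter the imputation model. Any effect by this path is probably small.

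The limitations in the Discussion acknowledge the greater contact time in the coaching arm as a source of performance and expectancy bias, but do not mention AE recording.

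**Working it through.** The plan gives no AE figure to reproduce. The check sets the sections side by side and then illustrates the possible size under stated assumptions. IG1 is the app with coaching, IG2 the app alone, CG usual care.

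**Step 1: routes by arm between T2 and T3**

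| Route | IG1 | IG2 | CG | Section |
|---|---|---|---|---|
| Coach documentation during the intervention | yes | yes | no | Randomization and blinding |
| Coach telephone interview at end of intervention | yes | yes | yes | Both sections |
| Assessor recording at T3 | yes | yes | yes | Both sections |
| Spontaneous reports | yes | yes | yes | Harms and safety monitoring (no arm restriction) |
| Weekly fall calendar (falls only) | yes | yes | yes | Secondary outcomes (no arm restriction) |
| Scheduled coach calls during the 12 weeks | three | none described | none | Personal coaching; Control |

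Only the first row separates the intervention groups from controls by rule. The last row suggests that this route may work mainly in IG1, so the IG1 v IG2 comparison may be affected too.

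**Step 2: length of recall in controls**

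T2 is nominally at week 6. The intervention starts nominally at week 8 and lasts 12 weeks, so it ends at 8 + 12 = week 20. The first scheduled AE contact for controls therefore looks back over 20 − 6 = 14 nominal weeks. T3 at week 26 looks back over a further 26 − 20 = 6 weeks.

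**Step 3: illustration of size (all rates assumed)**

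Let p be the true proportion with an AE, equal in all arms. Let s be the share captured by the routes common to all arms, and c the share of otherwise missed events that coach documentation recovers.

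- Recorded in controls: p × s
- Recorded in an intervention group: p × [s + (1 − s) × c]
- Apparent risk ratio: 1 + c × (1 − s)/s (p cancels)
- Apparent risk difference: p × c × (1 − s)

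| s | c | Risk ratio | Recorded, p = 0.20 (CG v IG) | Recorded, p = 0.40 (CG v IG) |
|---|---|---|---|---|
| any | 0 | 1.00 | no difference | no difference |
| 0.95 | 0.75 | 1 + 0.75 × 0.05/0.95 = 1.04 | 19% v 19.75% | 38% v 39.5% |
| 0.80 | 0.50 | 1 + 0.50 × 0.20/0.80 = 1.125 | 16% v 18% | 32% v 36% |
| 0.60 | 0.75 | 1 + 0.75 × 0.40/0.60 = 1.50 | 12% v 18% | 24% v 36% |

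With the planned 71 participants per group and p = 0.40, the third row is 71 × 0.32 = 22.7 against 71 × 0.36 = 25.6, about three participants. The last row is 17.0 against 25.6, between eight and nine. The direction is always towards more recorded events in the intervention groups.

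**The case against.** The strongest reply is that this is a wording difference, not a flaw in design. Randomization and blinding is there to say which recorders are blinded. Participants with a coach have someone to tell, so coach notes may simply be the spontaneous route of the harms section. The safety analysis is descriptive, an independent board assesses causality and severity, and tables by source are commonly left to the SAP.

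Much of this stands, and it rules out several stronger readings that a reader might infer:

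- **That control events in the 12 weeks go unrecorded.** They do not. The same sentence provides an end-of-intervention contact for all participants. T3, spontaneous reports and, for falls, weekly calendars are also open to controls.
- **That coaches question the intervention groups repeatedly.** The text says that events are documented, not that they are asked about. The description of the coaching calls mentions no AE enquiry. Counting five occasions (three calls, end call, T3) against two would treat every coaching call as an AE interview, and could apply to IG1 at most.
- **That the two sections flatly contradict each other.** One names a channel that the other omits. They can be read together, but staff cannot tell from them which scheme to follow.
- **That events from all sources will be pooled.** The analysis section does not say so.

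What the reply does not remove is the rule itself. The sentence contrasts both intervention groups with all participants, and so assigns an extra route by arm. That is a stated procedure, not a missing detail. A table by source in the SAP would help only if the source of each event had been recorded.

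**Conclusion.** The concern holds as a risk of ascertainment bias, not as a demonstrated bias. Followed as written, the plan collects AEs unequally during the intervention period, through unblinded staff, and its two sections on the matter do not match. Any between-arm summary of AE frequencies would lean towards more recorded events in the intervention groups, chiefly mild and moderate ones, possibly most in the coaching arm.

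The size cannot be determined from the article. The range of 1.00 to 1.50 for the apparent risk ratio rests on assumed capture rates and equal true risk. If the common contacts capture nearly all events (95%), it is at most 1.04 for recovery of up to 75%. The primary step-count comparison is not called into question. The point deserves correction because it is cheap to put right now and hard to repair later: events whose source was never noted may not be separable at analysis.

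**What to change.** 1. Reconcile Harms and safety monitoring with Randomization and blinding, so that both state the same routes for each arm and say whether coaches ask about AEs or only note what they are told.
2. Add a source field to the AE form (coach during the intervention, end-of-intervention call, T3, spontaneous report).
3. At the end-of-intervention call and at T3, put the same scripted questions to all arms, covering the whole period since randomization and expressly including events already reported. Without this, a participant who has told the coach may not repeat the event, and intervention-group harms would be under-counted.
4. Base the between-arm AE frequencies on events elicited at these two common contacts.
5. Also report all events from every source by arm, labelled as unequally ascertained. The safety board continues to see all of them.

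The cost is one form field, a short script and one more table. Some coach-noted events may appear only in the all-source table. The end-of-intervention call would still be made by unblinded coaches; a common script limits that problem but does not remove it. With 19 of 213 participants enrolled at submission and the SAP not due until before database closure, most of the trial could still run under the revised procedure.

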### Data collection and management

The Institute for Medical Biometry, Heidelberg University (IMBI) is responsible for data management within the study. Study data will be collected and managed using Research Electronic Data Capture (REDCap; [86]), a secure, web-based application that supports data entry with role-based access control, audit trails, and integrated data validation. Data transmission is encrypted (Secure Socket Layer, SSL), and access is restricted to authorized users with role-specific permissions. To ensure confidentiality, all data are pseudonymized, and changes are logged with time stamps in an audit file. Data validation rules are predefined in a data validation plan; data completeness, plausibility, and internal consistency are verified at the time of data entry using automated edit checks and additional validation programs that generate queries. Once all queries have been resolved and no further corrections are required, the database will be locked and released for statistical analysis. At the end of the study, data will be exported into reusable formats (e.g., CSV files) and archived by the principal investigator for long-term storage.

### Statistical analysis

For the first primary endpoint, the null hypothesis states that there is no difference in the mean daily step count at 6-months post-THA (T3) between IG1 and CG. The primary analysis will use linear regression at a two-sided significance level of 5%, adjusting for the stratification factor post-acute rehabilitation (outpatient, inpatient, or none) and preoperative mean daily step count. If this hypothesis is rejected, the subordinated primary endpoint (mean daily walking distance) at T3 between IG1 and CG will be tested (adjusted for post-acute rehabilitation and preoperative mean daily walking distance).

Subsequently, the following hypotheses will be tested hierarchically: IG2 (KOKU alone) vs. CG for mean daily step count at T3; IG2 vs. CG for mean daily walking distance at T3; IG1 vs. IG2 for mean daily step count at T3; and IG1 vs. IG2 for mean daily walking distance at T3. If any test in this sequence cannot be rejected, all subsequent tests will be considered exploratory only. This hierarchy reflects the assumption that IG1 (KOKU with PC) is at least as effective as, or superior to, IG2 (KOKU alone).

The primary analysis follows the intention-to-treat principle, with participants analyzed according to their randomized group. Intercurrent events are handled as follows: for non-compliance, additional interventions, AEs after randomization, new illnesses, or falls occurring between T2 and T3, a treatment-policy strategy (ICH E9 (R1)) will be applied, such that the estimated treatment effect includes the impact of these events. Death unrelated to the intervention will be handled under a hypothetical strategy, assuming the intervention does not affect the timing or occurrence of death within the observation window. If the T3 assessment cannot be performed due to a training-related injury or fatal event clearly attributable to the intervention, a “worst outcome” (step count = 0 steps/day, walking distance = 0 m/day) will be imputed as a composite strategy.

Missing values for primary endpoints due to dropout or loss to follow-up will be imputed under a missing-at-random (MAR) assumption using multiple imputations with predictive mean matching. The imputation model includes the stratification factor (post-acute rehabilitation type) and mean daily step count / mean daily walking distance at T1 and T2 for first and subordinated primary endpoints, respectively. Relevant intercurrent events, and other important prognostic variables will also be incorporated.

To investigate the robustness of the results, sensitivity analyses will be conducted, including adjustments for further potential confounders such as age and comorbidity burden, as well as a reference-based approach (“copy reference”) to explore departures from MAR under a missing-not-at-random (MNAR) scenario. The reference-based approach assumes that participants in the IGs with missing data gradually converge toward the outcome trajectory of the CG.

A supplementary estimand will be used to quantify treatment effects under alternative strategies, including hypothetical strategies for non‑compliance and composite strategies (“worst outcome”) for cases in which the T3 assessment cannot be completed for intervention‑related reasons. A predefined subgroup analysis will compare participants with higher vs. lower preoperative PA, as those with higher baseline PA may derive less additional benefit from the interventions.

Secondary endpoints will be analyzed descriptively using appropriate summary statistics and confidence intervals. Safety analyses will summarize absolute and relative frequencies of postoperative complications from randomization onward.

All planned analyses will be described in detail in the Statistical Analysis Plan, which will be finalized prior to database closure and any conduct of unblinded analyses.

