**Methods:**

In this monocentric, three-arm randomized controlled trial, 213 older THA patients (≥ 65 years) will be assigned in a 1:1:1 ratio post-rehabilitation to a 12-week digital home-based exercise program (“Keep On Keep Up”) with or without additional PC for PA promotion, or usual care. The primary outcome is the mean daily step count at six months post-THA; mean daily walking distance serves as a subordinated primary outcome. Both outcomes will be collected preoperatively, post-rehabilitation, and at six months postoperatively using a body-fixed inertial measurement unit (AX6, Axivity Ltd.) combined with newly validated processing algorithms (Mobilise-D computational pipeline). Secondary outcomes include other digital and self-reported mobility outcomes, physical capacity, hip pain and function, psychological factors, falls, intervention acceptability, and health-related resource use. Primary analyses will follow the intention-to-treat principle.

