## Methods

### Study design and setting

The iPATH study (“Digital home-based Physical Activity promotion for older adults after Total Hip arthroplasty”) is a three-arm, assessor-blinded, randomized, parallel-group, monocentric, superiority trial with a 12-week intervention period. Outcomes are assessed 1 week preoperatively (T1), 6 + 2 weeks postoperatively (T2), and 6 months postoperatively (T3; 26 ± 2 weeks). Participant recruitment and on-site outcome assessments will take place at the Department of Orthopaedics, Heidelberg University Hospital, Heidelberg, Germany. Participants will be randomly allocated after T2 to one of two intervention groups (IG) or the control group (CG). The digital interventions will be delivered remotely and implemented at participants’ homes, starting 8 ± 2 weeks after THA following completion of the standard rehabilitation phase. The study flowchart is shown in Fig. 1. The trial was preregistered at ClinicalTrials.gov (NCT07135843) on August 22, 2025. This protocol is reported in accordance with the Standard Protocol Items: Recommendations for Interventional Trials (SPIRIT) guidelines [36].

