Following the initial screening, the study team will verify and complete the eligibility assessment, including cognitive screening using the Six-Item Cognitive Impairment Test [37], and assessment for presence of contralateral coxarthrosis requiring THA. Patients with bilateral coxarthrosis requiring THA on both sides will be placed on a waiting list, and participation may be reconsidered at subsequent surgery if a minimum interval of three months between procedures is met. Patients with coxarthrosis without a current indication for THA will likewise be placed on the waiting list and may be re-screened and enrolled later if a surgical indication arises.

Eligible patients will receive detailed verbal and written information about the study objectives, procedures, potential benefits, and risks. Written informed consent will be obtained preoperatively (T1) by medical staff, following renewed explanation and an adequate reflection period. Formal study inclusion and the T1 assessment will proceed only after informed consent has been obtained.

Approximately four weeks after THA, a postoperative screening will be conducted via telephone to confirm continued study eligibility by verifying ability to walk 10 m with or without walking aid, completion of post-acute rehabilitation, and the absence of postoperative complications that would preclude initiation of the digital exercise program within the following four weeks (Table 1). Only participants who maintain eligibility will proceed to the 6-week postoperative assessment (T2) and randomization.

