#### Primary outcomes

The first primary outcome is the mean daily step count, and the subordinated primary outcome is the mean daily walking distance. Both DMOs will be recorded with a small (23.0 × 32.5 × 8.9 mm) and lightweight (11 g), water-resistant 6-axis inertial measurement unit (IMU; AX6, Axivity Ltd., Newcastle upon Tyne, United Kingdom), fixed at the participant’s lower back (L5 vertebra) using self-adhesive fixing foil, over a maximum measurement period of 7 consecutive days subsequently to the on-site assessments. After the measurement period, participants will remove the IMU themselves and return it to the study center in a prepaid, pre-addressed envelope. The IMU will be configured with a tri-axial accelerometer (range ± 8 g, accuracy 1 mg) and a tri-axial gyroscope (range ± 2000 dps, resolution 70 mdps), with a sampling frequency of 100 Hz. Raw data from the IMU will be standardized according to a predefined data structure described elsewhere [50]. The Mobilise-D computational pipeline (available at https://github.com/mobilise-d/mobgap), which consists of validated algorithms to derive DMOs [51–53], will then be used to identify WBs [54] and extract number of steps, duration, walking speed, stride length, cadence, and stride duration for each of these WBs. Walking distance per WB will be calculated by multiplying two validated DMOs: average walking speed × WB duration [55]. Steps and walking distances at the WB level will then be aggregated to daily level and averaged across up to 7 valid measurement days to yield mean daily step count and mean daily walking distance. A valid measurement is defined as ≥ 3 valid measurement days; a valid measurement day is defined with ≥ 12 h/day of wear time during waking hours (7 am – 10 pm), without weekday/weekend restriction [56].

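### The primary regression adjusts for the preoperative value only; adding the T2 value, already collected at the assessment that precedes randomisation, would buy precision at little cost, though how much is unknown.

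*Protocol article*

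**What the plan says.** The Statistical analysis section of the protocol article specifies the first primary test (IG1 versus CG, mean daily step count at T3) as a linear regression "adjusting for the stratification factor post-acute rehabilitation (outpatient, inpatient, or none) and preoperative mean daily step count". The second test, on mean daily walking distance, is "adjusted for post-acute rehabilitation and preoperative mean daily walking distance". Tests 3 to 6 are listed in order without covariates.

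Both outcomes are also measured between those two time points. The abstract states: "Both outcomes will be collected preoperatively, post-rehabilitation, and at six months postoperatively using a body-fixed inertial measurement unit". Table 2 marks step count and walking distance at T1, T2 and T3. Under Randomization and blinding: "After the 6-week postoperative assessment (T2), participants will be randomized to one of three study arms". The imputation model for missing primary endpoints includes "mean daily step count / mean daily walking distance at T1 and T2". The sensitivity analyses name age and comorbidity burden as further covariates, not T2. No reason is given for leaving T2 out of the regression.

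On timing, the Primary outcomes section says the sensor is worn "over a maximum measurement period of 7 consecutive days subsequently to the on-site assessments". T2 falls at 6 + 2 weeks after surgery, and the interventions start at 8 ± 2 "weeks after THA following completion of the standard rehabilitation phase".

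**The concern.** The trial tests an intervention that begins after surgery and rehabilitation. T1 is recorded on the diseased hip before either. T2 is recorded after both, with the same sensor and pipeline, and is the last assessment before allocation. It can carry information about each participant's response to surgery and rehabilitation that T1 cannot, and the authors treat it as informative enough to use for imputation. Leaving an available baseline value of the endpoint out of the analysis model usually widens the confidence interval for no saving.

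At stake is efficiency, not validity. The gain would matter most late in the testing sequence. The sample size is derived for IG1 versus CG only, and the authors expect IG1 to exceed IG2 and both to exceed CG, so the remaining contrasts should be smaller.

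A related gap decides whether T2 is usable. The T2 recording starts after the on-site visit and can run for a week, and the text does not say that allocation waits for it to end.

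**Working it through.** **Inputs from the documents (Sample size).** SD 3,000 steps/day; difference 1,500 steps/day; two-sided 5%; 80% power; 64 per group before dropout; independent-samples t-test.

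**Inputs that are assumptions.** The documents give no correlations between T1, T2 and T3. Write r12, r13 and r23 for T1-T2, T1-T3 and T2-T3. I take r13 = r12 = 0.5 and let r23 run from 0.4 to 0.7. The SD of 3,000 is stated for preoperative steps and is carried over to T3, as the sample size calculation does.

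**Step 1, the plan's own figure.** d = 1,500/3,000 = 0.5. The noncentral t gives power 79.5% at 63 per group and 80.1% at 64. The stated 64 reproduces. No covariate enters this calculation.

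**Step 2, T1 only.** The residual variance fraction is 1 − r13² = 1 − 0.25 = 0.750. The residual SD is 3,000 × √0.750 = 2,598, and power at 64 per group for 1,500 steps is 0.90. The T1 adjustment alone already lifts power above the planned 80% under this assumption.

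**Step 3, T1 and T2.** R² = (r13² + r23² − 2·r13·r23·r12)/(1 − r12²). For r23 = 0.6: (0.25 + 0.36 − 0.30)/0.75 = 0.413, leaving 0.587. The ratio to T1 only is 0.587/0.750 = 0.782, and interval width scales with its square root, 0.884.

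| r23 | Residual variance | Cut against T1 only | Narrower interval | Power, 1,500 steps |
|---|---|---|---|---|
| T1 only | 0.750 | – | – | 0.90 |
| 0.4 | 0.720 | 4% | 2% | 0.91 |
| 0.5 | 0.667 | 11% | 6% | 0.93 |
| 0.6 | 0.587 | 22% | 12% | 0.96 |
| 0.7 | 0.480 | 36% | 20% | 0.98 |

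**Step 4, a smaller effect.** The documents state no effect for the later contrasts. For an illustrative 1,000 steps, power is 0.58 with T1 only and 0.60, 0.63, 0.69 and 0.77 down the four rows.

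**Step 5, when the gain vanishes.** The variance ratio equals 1 minus the squared partial correlation of T2 and T3 given T1. That partial correlation is zero when r23 = r12 × r13. With r12 = r13 = 0.7 the product is 0.49, and r23 = 0.5 gives a gain of 0%. Over a wider grid (r12 and r13 from 0.4 to 0.7, r23 from 0.4 to 0.8) the interval narrows by 0% to 39%.

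**Step 6, timing.** The T2 visit falls in weeks 6 to 8 and the recording adds up to 7 days. The intervention start window is weeks 6 to 10. The windows overlap. After randomisation comes a home visit with arm-specific instructions and, in the coaching arm, an activity tracker. The text neither places the end of the recording before allocation nor says the opposite.

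**The case against.** The strongest reply is that nothing here is wrong. A T1-adjusted regression is prespecified and unbiased and holds its type I error. The design power does not depend on any covariate. The size of the gain is assumed: a range that sets T2-T3 above T1-T3 presupposes that T2 is the better predictor. T2 comes early in recovery, and the Background section itself says that low preoperative activity often persists after surgery, which is a reason to value T1. And if some T2 days fall after allocation, adjusting for them could bias the effect, whereas T1 is safely before randomisation.

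Most of this stands and limits the point. It does not remove it: adding a true baseline covariate costs one model parameter, and the timing risk is met by fixing the order of recording and allocation.

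Several stronger readings are tempting but unsupported:

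- A reader might infer that the trial is underpowered or its primary test biased. Neither follows.
- A reader might say the T2 data are discarded. They are used for imputation.
- A reader might say T2 is left out of all six tests. Covariates are stated only for tests 1 and 2.
- A reader might conclude that T2 is recorded after randomisation. The wording is ambiguous, since allocation after T2 could include the sensor week.
- A reader might point to waiting-list patients, whose T1 could follow a contralateral replacement "if a minimum interval of three months between procedures is met". The documents do not say how many there will be, so this adds nothing measurable.

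**Conclusion.** The point holds as a worthwhile, low-cost gain in efficiency. The primary model leaves out a baseline value of the endpoint that the trial already collects and already uses for imputation. Validity and the planned 80% power are unaffected.

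The benefit cannot be fixed from the documents. The 4% to 36% cut in residual variance rests wholly on the assumed correlations, and a gain close to zero is possible. The documents do not establish that T2 is a strong predictor; that is plausible, no more. The recommendation also depends on T2 being recorded before allocation, which the text should state.

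**What to change.** Before unblinding, prespecify for tests 1 and 2: T3 value ~ arm + rehabilitation type + T1 value + T2 value, with step count adjusted for step counts and walking distance for walking distances. State the same model for tests 3 to 6, whose covariates are not given. Keep the T1-only model as a sensitivity analysis.

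Add one sentence to the randomisation procedure: allocation is released only after the T2 recording has ended. Recruitment began in September 2025 and 19 participants were enrolled at submission, so some may already have been randomised. For anyone already randomised, compare recording and allocation dates, use only T2 days recorded before allocation, and multiply impute T2 where too few remain. The protocol's own threshold of three valid days can serve as the criterion.

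The cost is a wording change, one extra model parameter, a few days' delay to allocation and a date check for those already randomised. No new measurement is needed. The analysis plan is still to be finalised before unblinded analyses, so the change can be made cleanly.
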